### Measurement of rSO_2_

#### Necessity

The brain is the most metabolically active organ in the body and one of the main sites of action of anesthetic drugs, and the risk of internal homeostatic imbalance and postoperative dysfunction exists after surgery. The brain, the main organ of the central nervous system in our body, is complex and fragile. Although it accounts for only 2–3% of the total body weight, it consumes 15–20% of the standard cardiac output and 20–25% of the whole-body oxygen content. The brain is a highly metabolic, high-oxygen-consuming organ, increasing its sensitivity to hypoxia. The brain is susceptible to various adverse prognostic reactions, including semicoma, coma, sudden illness, memory loss, and intellectual disability. However, most cerebral hypoxic events are difficult to monitor effectively with currently available equipment, and thus the damage to the brain is often long-established by the time the hypoxic event is detected.

Furthermore, as a common consensus, the available research evidence supports that cerebral ischemia and hypoxia may be direct causes of neurocognitive impairment and may play essential roles in the pathophysiological mechanisms of POCD, AD, and neurodegenerative diseases. For example, hypoxia induces the activation of various factors, reduces the cerebrovascular reserve, and exacerbates excitotoxicity and neuroinflammation [52, 53]. The *“2020 American Society for Enhanced Recovery and Perioperative Quality Initiative”* issued a joint consensus statement on the use of perioperative cerebral oxygen monitoring techniques [54] summarizing relevant studies on preoperative baseline rSO_2_ values and postoperative outcomes, and suggested a correlation between low baseline rSO_2_ values and adverse outcomes, such as postoperative neurocognitive impairment, increased 30-day all-cause mortality, and prolonged hospital discharge. The importance and necessity of perioperative cerebral oxygen saturation monitoring are further recommended.

#### Equipment

The determination of rSO_2_ using NIRS to estimate the oxygen saturation of hemoglobin in brain tissue was first developed in the late 1970s [55] and became commercially available with the introduction of the NIRO-1000 by Hamamatsu Corporation (Iwata, Shizuoka, Japan) in 1989 [56]. With additional clinical research evidence in recent years, the clinical relevance and feasibility of using cerebral oximetry to detect adverse perioperative clinical events and guide patient care in cardiac and noncardiac surgical settings have been initially confirmed [57, 58]. However, NIRS devices from multiple manufacturers differ in wavelength, wavelength number, sensor configuration, and proprietary integration algorithms used to determine brain saturation. Differences between devices make their final measured values not directly interchangeable in equal amounts. The FORE-SIGHT Oximeter (Fig. 2) will be used in this study. Thus, we will briefly explain the corresponding principles of the function and operating methods below.

**Fig. 2 Fig2:**
[figure not shown]
FORE-SIGHT cerebral oxygen monitor and sensors (The copyright of Fig. 2 belongs to *Beijing Gloryway Medical Co., Ltd*, and we have obtained the associated permissions)

### Function principles

The FORE-SIGHT measurement method has essential features such as noninvasiveness, continuity (data updated once every two seconds), and the construction of rSO_2_ trend maps (comparison of differences between the left and right hemispheres of the brain) on both sides of the brain. The sensor is available in three sizes, large, medium, and small (Fig. 2), it is adapted to adults, children, and newborns, and the appropriate sensor can be selected for each group relative to the patient's weight. The sensor detects the difference in the absorption of oxyhemoglobin and deoxyhemoglobin using a laser that emits four bands of near-infrared light that penetrate the scalp, skull, and brain tissue, thus measuring the mixed arterial-venous oxygen saturation of the brain tissue. Hemoglobin is a known carrier with oxidation and de-oxidation characteristics, and the degree of oxygen saturation of brain tissue depends on the proportion of oxyhemoglobin in total hemoglobin. The NIRS technique uses laser wavelengths to estimate the ratio of oxyhemoglobin to total hemoglobin by absorbing the fully and partially oxidized hemoglobin molecules differently. The specific algorithm is extremely complex and we will not go into details here (water and hemoglobin are different in human tissue absorption spectra, hemoglobin can be detected at 650 nm—900 nm) (Fig. 2).

### Operating method

In this study, we will use a FORE-SIGHT regional oximeter (CAS Medical Systems, Inc.) to collect rSO_2_. This regional oximeter monitors intracerebral rSO_2_ using NIRS and reflectance oximetry, displaying absolute rSO_2_ values and trends. Absolute oximetry values will be defined as rSO_2_ measured with an oximetry probe calibrated with a fixed arterial-to-venous blood ratio. In our study, only absolute oximetry data will be extracted and analyzed. We will install NIRS sensors on each side of the patient's forehead and measure rSO_2_ in both brain hemispheres. Baseline rSO_2_ will be recorded before the start of any medication and before induction of anesthesia, and subsequent rSO_2_ measurements will be recorded every 10 s until the last surgical suture is complete. At the end of the procedure, the data for the entire test cycle will be read via a memory stick through the USB port on the instrument. Moreover, the data collected (within the first two hours of surgery) will finally be presented as a line graph with data visualization software (GraphPad Prism) to visualize the temporal trend of changes in rSO_2_ in both hemispheres. Although we will perform dynamic acquisition of rSO_2_ values throughout the procedure for each patient, the visualization will be limited to 2 h after the start of the procedure due to the substantial variation in the time of the procedure between patients. The absolute change in percent change in rSO_2_ will be calculated by subtracting the baseline rSO_2_ value (T_0_) from the value measured at the end of the procedure (T_4_), multiplied by 100%. The investigators will collect rSO_2_ data from the sensors placed on the patient's left and right forehead.

### Measurement of PNDs

In 2018, a multidisciplinary expert working group on perioperative cognitive nomenclature standardized the terminology for cognitive changes associated with anesthesia and surgery [59], recommending the term "*perioperative neurocognitive disorders (PNDs)"* to describe patients with perioperative cognitive changes. The acronym PNDs is more relevant and reasonable based on the multidisciplinary consensus in neurology and the specialty of anesthesia on neurocognitive disorders. Further distinctions are made according to the point of onset and severity of cognitive impairment: (1) *Preexisting NCD*: a measurable, objective cognitive impairment that exists preoperatively; (2) *Postoperative delirium (POD)*: occurring within one week of surgery or before discharge and meeting the Diagnostic and Statistical Manual of Mental Disorders-5 (DSM-5) criteria for delirium; (3) *Delayed neurocognitive recovery (DNR)*: a cognitive impairment that exists within 30 days of surgery; (4) *Postoperative NCD*: cognitive impairment present from 30 days to 12 months postoperatively. It was also divided into *postoperative mild NCD* and *major postoperative NCD* according to the degree of cognitive impairment. (5) Cognitive impairment first diagnosed more than 12 months after surgery is referred to as *mild NCD* and *severe NCD*, depending on its severity, without the qualifier "postoperative" because it is difficult to determine whether the cognitive impairment occurring at this time is causally related to the previous anesthesia and surgery. The combination of delayed neurocognitive recovery, the cognitive decline within 30 days of surgery, and cognitive decline between 30 days and 12 months after surgery correspond to our traditional definition of "*postoperative cognitive dysfunction (POCD)*." In this study, the MMSE will be used to measure the occurrence of DNR in patients 1 d before and 1, 3, and 7 d after surgery, respectively (Table 2).

**Table 2 Tab2:** Postoperative cognitive outcome and perioperative brain injury marker testing

**Variables**	MMSE	DNR	NSE	IL-6
Preoperative 1 d	**√**	**√**	**√**	**√**
Postoperative 1 d	**√**	**√**	**√**	**√**
Postoperative 3 d	**√**	**√**	**/**	**/**
Postoperative 7 d	**√**	**√**	**/**	**/**

*DNR* Delayed Neurocognitive Recovery, *MMSE* Mini-mental State Examination, *NSE* Neuron Specific Enolase, *IL-6* Interleukin-6

The MMSE is one of the most influential and popular international screening instruments for cognitive impairment, covering time, place orientation, immediate memory, attention, computation, short-term memory, language, and visuospatial structure skills. However, a capping and learning effect exists for the MMSE. The MMSE is insensitive to subtle changes in cognitive function that may occur after surgery. Thus, the MMSE is more suitable for preoperative screening in PND studies. The MoCA covers a broader range of cognitive domains than the MMSE, which makes it seems to be more accurate and sensitive than the MMSE for the determination of mild cognitive impairment. But our previous pilot study showed that the MoCA is too difficult and time-consuming to implement. Therefore, we will choose the MMSE as the assessment tool for postoperative cognitive function outcome (The patients with postoperative MMSE score ≤ 23 and a decrease of more than 2 points from the baseline value were defined as DNR). In addition, as a secondary outcome measure, we can accept the limitations of the MMSE.

### Measurement of PaCO_2_ and arterial blood gas analysis

Immediately after tracheal intubation, the minute ventilation will be adjusted to achieve PETCO_2_ concentrations of 45–55 mmHg in Group H and 35–40 mmHg in Group N. Due to the presence of alveolar dead space, PETCO_2_ maybe 5 mmHg-10 mmHg lower than PaCO_2_, and thus we will measure PaCO_2_ by performing an arterial blood gas (ABG) analysis and further adjust ventilation to achieve the desired PaCO_2_ target range. In addition, we will set 7.2 as the lowest pH limit for Group H. PaCO_2_ and the PETCO_2_ gradient will be maintained at constant levels as much as possible throughout the procedure. If the concentration of PaCO_2_ must be reassessed, for example, ventilation settings must be adjusted, additional ABG samples will be collected at the discretion of the anesthetist. Finally, at the end of the procedure, ABG samples will be collected to record PaCO2 values accurately and to assess whether PaCO_2_ is maintained within target values.

The Roche Cobas b 123 blood gas analyzer measures pH, PaCO_2_, Na^+^, K^+^, Cl^−^, Ca^+^, erythrocyte pressure (Hct), and metabolites (Glu and Lac) in whole blood using a selective motor technique. The pH, PaCO_2_, Na^+^, K^+^, Cl^−^, and Ca^+^ will be measured using the potentiometric method, erythrocyte pressure will be measured using the conductivity method, and PaO_2_ and metabolites will be measured using the current method. The built-in blood gas analyzer module measures total hemoglobin (tHb), hemoglobin derivatives (O_2_Hb, HHb, COHb, and MetHb), oxygen saturation (SO_2_), and bilirubin (Bili) levels using spectrophotometric methods. Notably, sodium heparin is the only anticoagulant allowed for use in the analysis with the Cobas b 123 system. Other anticoagulants, such as citrate, oxalate, fluoride, and ammonia-containing anticoagulants, exert significant effects on blood pH and other parameters and, therefore, should not be used. In addition, blood used for the analysis must be collected from the blood vessels of eligible persons. Under no circumstances should pressure be applied to the puncture site because the blood will begin to clot prematurely if the blood sample is mixed with tissue fluid, even if the sample collection vessel is adequately heparinized. The specimen should be sent for analysis immediately after collection and, in principle, should be tested within 15 min.

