## Methods

### Study design, setting and participants

Between October 2022 and July 2023, we plan to conduct an RCT at Shengjing Hospital of China Medical University (Shenyang, China), a university teaching, higher education, large general hospital. The trial period is expected to be 10 months, during which patient recruitment, intervention implementation, and postoperative follow-up will be conducted in an orderly manner according to the actual situation. The final results are expected to be reported in October 2023. Participants will be screened from the patients proposed for elective laparoscopic colorectal surgery in the gastrointestinal surgery department of the hospital. Patients who are eligible for elective major surgery are identified after a preoperative evaluation and receipt of written informed consent before the patient's surgery date. Patients who meet the screening criteria will be randomly assigned 1:1 to the control group (Conventional ventilation group parameters: Tidal volume10 ~ 12 mL/kg, Respiratory rate 14 ~ 16 bpm, Suction/Respiration ratio 1:2, PaCO_2_ 35 ~ 45 mmHg, PEEP 0 cmH_2_O, FiO_2_ 40%) and the intervention group (Permissive hypercapnia group parameters: Tidal volume 6 ~ 8 mL/kg, Respiratory rate 12 ~ 14 bpm, Suction/Respiration ratio 1:2, PaCO_2_ 45 ~ 55 mmHg, pH > . 7.2, PEEP 0 cmH_2_O, FiO_2_ 40%), and 38 patients will be included in each group. Baseline preoperative rSO_2_ values will be recorded, and real-time intraoperative rSO_2_ monitoring will be performed by investigators who are not providing the clinical intervention. In addition, patients will be followed up postoperatively with MMSE scale to assess early postoperative cognitive function. The patients with postoperative MMSE scores ≤ 23 and a decrease of more than 2 points from the baseline value were defined as delayed neurocognitive recovery (DNR). It should be noted that the follow-up personnel have received standardized training in advance, to ensure that the survey scale can be used scientifically and correctly (Fig. 1).

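### Group H's starting PETCO2 window repeats its PaCO2 target and leaves no room for the 5–10 mmHg gradient the protocol itself describes

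*Protocol article*

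**What the plan says.** The section *Study design, setting and participants* defines the arms by arterial CO2: "PaCO_2_ 45 ~ 55 mmHg" for the permissive hypercapnia arm (H) and "PaCO_2_ 35 ~ 45 mmHg" for the control arm (N).

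The section *Measurement of PaCO2 and arterial blood gas analysis* turns this into a ventilator instruction. It opens "Immediately after tracheal intubation, the minute ventilation will be adjusted to achieve" and gives the values "PETCO_2_ concentrations of 45–55 mmHg in Group H and 35–40 mmHg in Group N". It then notes that, because of alveolar dead space, "PETCO_2_ maybe 5 mmHg-10 mmHg lower than PaCO_2_, and thus we will measure PaCO_2" by ABG and "further adjust ventilation to achieve the desired PaCO_2_ target range". Group H also has a pH floor of 7.2. Further gases are optional: "additional ABG samples will be collected at the discretion of the anesthetist". On turnaround, a specimen "in principle, should be tested within 15 min".

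The first gas with a printed time is the one at T1, 15 minutes after intubation (*Secondary endpoints*; *Collection and analysis of venous blood samples*). *Randomization and blinding* names PETCO2 as the quantity set to deliver the intervention. *Anesthesia maintenance* and the *Discussion* make PaCO2 the governing target thereafter.

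**The concern.** End-tidal and arterial CO2 are different quantities, and the protocol says by how much they may differ. A PETCO2 window meant to deliver a PaCO2 target should sit below that target. Group N's does in part: its window ends at 40 and its PaCO2 ceiling is 45. Group H's window and target are identical, and no reason is given for treating the arms differently.

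The CO2 level is the treatment, and patients are enrolled because of fragile brain function. A starting instruction that permits values above the protocol's own ceiling is therefore worth correcting even if the period is short. T1 is also a data point: rSO2, Da-jvO2 and CERO2 at T1 are secondary endpoints. If no gas has been acted on before T1, those readings come from the unadjusted starting setting.

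**Working it through.** **Inputs**
- PETCO2 windows: H 45–55, N 35–40 mmHg (*Measurement of PaCO2 and arterial blood gas analysis*).
- PaCO2 targets: H 45–55, N 35–45 mmHg (*Study design, setting and participants*).
- Gradient g = PaCO2 − PETCO2: 5–10 mmHg, stated as a possibility (*Measurement of PaCO2 and arterial blood gas analysis*). Smaller values of g are included below because of that wording.

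**Step 1: implied PaCO2 = PETCO2 + g**
- H: 45 + 5 = 50 up to 55 + 10 = 65, against a target of 45–55.
- N: 35 + 5 = 40 up to 40 + 10 = 50, against a target of 35–45.

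**Step 2: highest PETCO2 still in target = ceiling − g**
- H: 55 − 5 = 50 at g = 5, so only the lower half of the window complies. At g = 10 it is 45, so only the bottom value complies.
- N: 45 − 5 = 40 at g = 5, so the whole window complies. At g = 10 it is 35.

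**Step 3: overshoot of the PaCO2 ceiling at the top of the window**
- H as printed: (55 + g) − 55 = g.
- N as printed: max(0, (40 + g) − 45) = max(0, g − 5).
- H with 45–50: max(0, (50 + g) − 55) = max(0, g − 5), the same as N.

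| g (mmHg) | 0 | 2.5 | 5 | 7.5 | 10 |
|---|---|---|---|---|---|
| H overshoot, printed 45–55 | 0 | 2.5 | 5 | 7.5 | 10 |
| N overshoot, printed 35–40 | 0 | 0 | 0 | 2.5 | 5 |
| H overshoot, with 45–50 | 0 | 0 | 0 | 2.5 | 5 |
| H PaCO2 range, with 45–50 | 45–50 | 47.5–52.5 | 50–55 | 52.5–57.5 | 55–60 |

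**Step 4: midpoint contrast between arms, with a common gradient**
- PaCO2 targets: 50 − 40 = 10.
- Printed PETCO2 windows: 50 − 37.5 = 12.5.
- H 45–50 with N 35–40: 47.5 − 37.5 = 10.

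**Step 5: possible duration**
If the first gas is the T1 gas, it is drawn at 15 minutes. If testing takes the full 15 minutes, the result arrives by 15 + 15 = 30 minutes. If the ABG promised after the initial setting is taken sooner, the period is shorter. The protocol gives no time for that ABG.

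**The case against.** The strongest reply is that the protocol answers the point in its next sentence. It gives the gradient as the reason for measuring PaCO2 and adjusting ventilation. That ABG is a commitment; only the additional samples are discretionary. PETCO2 is then a first setting and PaCO2 governs. This largely stands, and it is why the point is minor. It does not explain why the first setting in Group H ignores a gradient that Group N's partly allows for. The pH floor does not cover the gap either, because pH is read from the same gas.

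A reader might go further in four ways that the documents do not support.
- **Group H is held at up to 65 mmHg for 15–30 minutes.** This needs the top of the window, the largest gradient, prompt attainment and no gas before T1. The gradient is worded as a possibility, the *Background* speaks of easing patients into the acidic state, and an ABG before T1 is not ruled out. The exposure is possible, not shown.
- **The T1 secondary readings reflect the uncorrected setting.** This is true only if no gas was acted on beforehand, which is not stated.
- **Correcting PaCO2 forces PETCO2 below 45.** That follows only if 50 is the aim and the gradient exceeds 5. The protocol targets the range 45–55, and for every gradient from 0 to 10 some PETCO2 within 45–55 meets it.
- **The primary result is compromised.** It is read at T4, after the T1–T3 gases, and the printed windows do not shrink the contrast between arms.

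A larger correction, Group H at 40–45, would keep PaCO2 in target for all gradients from 5 to 10. However, it cuts the midpoint contrast before the first gas to 42.5 − 37.5 = 5 mmHg, half of the intended 10. At a gradient of 0 it also puts Group H at 40–45, inside Group N's target. That is a clinical trade-off rather than a clear improvement.

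**Conclusion.** The mismatch is real and minor. Group H's initial PETCO2 window copies its PaCO2 target. If the gradient is 5–10 mmHg, as the protocol says it may be, the window implies PaCO2 of 50–65, and any PETCO2 above 50 exceeds the ceiling of 55. At the top of the window the excess equals the gradient, 5–10 mmHg, compared with 0–5 mmHg in Group N.

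The consequence is limited to the time before the first ABG, which has no fixed time unless it is the T1 gas, and possibly to the T1 secondary readings. The T4 primary endpoint and the PaCO2-governed maintenance are not shown to be affected. The size rests on the protocol's own gradient and on patients being ventilated in the upper part of the window; at a gradient of 0 there is no overshoot.

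**What to change.** In *Measurement of PaCO2 and arterial blood gas analysis*:
1. Print Group H's initial PETCO2 window as 45–50 mmHg, parallel to Group N's 35–40, which stays as it is.
2. State that both windows are provisional until the first ABG.
3. Take that ABG from the arterial line before the T1 readings.
4. From then on, in both arms, set PETCO2 to the PaCO2 target minus the gradient measured at that ABG. For Group H this gives 40–50 at a gradient of 5 and 35–45 at a gradient of 10.

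The cost is one changed number, a few sentences, and at most one earlier sample from a line the protocol already provides. The downsides are a narrower starting window and, at gradients above 5, some remaining overshoot (up to 5 mmHg at a gradient of 10) until the first gas is acted on.

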### Collection and analysis of venous blood samples

Venous blood samples are collected for two primary purposes: one is for blood gas analysis, and in collaboration with the ABG analysis at four-time points from T_1_ to T_4_, the CERO_2,_ and Da-jvO_2_ at the four-time points will be calculated using the Fick formula. The second objective is to determine brain injury marker levels to explore whether the interventions affect them and their association with postoperative cognitive function outcomes.

*Fick formula*:$$CaO2=Hb\times 1.36\times SaO2+0.0031\times PaO2$$$$CjvO2=Hb\times 1.36\times SjvO2+0.0031\times PjvO2$$$$Da-jvO2= CaO2-CjvO2$$$$CERO2:\left(CaO2-CjvO2\right)\div CaO2\times 100\%$$

*(CaO*
_*2*_
*, SaO*
_*2*_
*, and PaO*
_*2*_
* are arterial oxygen content, arterial oxygen saturation, and arterial oxygen partial pressure, respectively; CjvO*
_*2*_
*, SjvO*
_*2*_
*, and PjvO*
_*2*_
* are internal jugular venous oxygen content, internal jugular venous oxygen saturation, and internal jugular venous oxygen partial pressure, respectively; Hb represents hemoglobin concentration.)*

Venous blood samples will be collected from the bulb of the jugular vein preoperatively (after induction of anesthesia and before the start of surgery) and 24 h postoperatively, and the serum IL-6 and NSE concentrations will be measured using ELISAs. After the induction of anesthesia, a puncture will be made through the middle of the right internal jugular vein in the direction of the distal end, and a tube will be placed under ultrasound guidance in the reverse direction up to the bulb of the jugular vein for blood sample collection. The resistance encountered, and the depth of 15 cm will be used as the markers for entering the jugular vein bulb. Before and after the operation, 4 mL of blood samples will be collected from the bulb of the jugular vein and then centrifuged at 4000 r/min for 10 min at 4 °C after 30 min of incubation.

### NSE

NSE in the cytoplasm of neurons and neuroendocrine cells has the primary function of participating in glycolysis and catalyzing the production of phosphoenolpyruvate. Under normal conditions, the level of NSE in body fluids is shallow. However, following nerve cell injury, a large amount of NSE leaks from the intracellular space to the intercellular space and enters the cerebrospinal fluid and blood circulation. Therefore, an increase in the NSE level in body fluids indicates nerve cell damage and can be used as an essential predictor to determine the extent of neuronal damage [60]. NSE is a marker of neurons and neuroendocrine cells, with levels ranging from high to low in the brain, spinal cord, and peripheral ganglia. NSE accounts for 1.5% of all soluble proteins in the brain and is present at much lower levels in peripheral nerves than in brain tissue. Hans et al. [61] confirmed that NSE release was significantly and positively correlated with the number of dead neuronal cells but not with glial cells. Thus, in individuals with acute cerebrovascular diseases, such as cerebral hypoxia–ischemia, cerebral hemorrhage, and cerebral edema, the main pathological changes resulting from the injury are necrosis of neurons and disintegration of neurospinal phospholipid, and the NSE in the cytoplasm of necrotic neurons will be released directly into the cerebrospinal fluid (CSF), which increases the concentration of NSE in the CSF and subsequently leaks into the plasma through the damaged blood-cerebrospinal fluid barrier, all of which have been confirmed by animal experiments [62]. In addition, a comparison of blood and CSF specimens showed that serum NSE measurements replace CSF measurements and that the serum NSE level is a sensitive indicator of brain parenchymal damage [63]. Notably, Rasmussen et al. measured NSE levels in perioperative serum samples and assessed preoperative and postoperative cognitive function in 15 patients undergoing coronary artery bypass grafting, which concluded that an increase in serum NSE levels were strongly associated with early postoperative cognitive dysfunction [64].

